### Participant withdrawal

Participants will be informed that they have the right to withdraw from the trial at any time. Participants who are withdrawn will not be replaced. If withdrawal occurs within 28 days after vaccination, and if agreeable, the participant will continue to be contacted by telephone at expected visits to confirm AE or SAE status.

The investigator will discontinue vaccination if the participant experiences any SAE related to the administration of the previous vaccine, including an anaphylactic or other significant allergic reaction. In addition, a participant may be withdrawn from the study if, in the investigator’s judgement, there are safety concerns, or significant noncompliance with the study protocol. If a participant experiences an AE or SAE considered by the investigator to be related to vaccination, the participant will be followed until the condition resolves or becomes stable.

### Primary outcome

The primary outcome is the percentage of participants with seroprotection (HI titre ≥1:40) at day 208 post primary vaccination for each of the influenza strains present in the administered influenza vaccine.

### Secondary outcomes

The secondary outcomes are as follows:Comparison by vaccination group of Geometric Mean Titres (GMTs) against homologous and heterologous influenza strains from day 208 to day 360Comparison by vaccination group of the Geometric Mean Ratio (GMR) of HI titres post versus pre-vaccination (day 1), against homologous and heterologous strains from day 208 to day 360Comparison by vaccination group of seroprotection rates (HI titre ≥1:40) against homologous and heterologous strains from day 208 to day 360Comparison by vaccination group of participants with seroconversion against homologous and heterologous strains from day 208 to day 360 (seroconversion is defined as a pre-vaccination (day 1) HI titre <10 and post-vaccination HI titre ≥40 or at least a four-fold increase in HI titres from a pre-vaccination HI titre ≥10)Comparison by vaccination group of MN titres against homologous and heterologous strains from day 208 to day 360Number of participants reporting ILI across vaccine groups from day 208 to day 360Number of participants with PCR-confirmed influenza across vaccine groups from day 208 to day 360Number of participants reporting healthcare utilisation (emergency room visits, unscheduled physician visits, and hospitalisations in each group) across vaccine groups from day 180 to day 360All-cause mortality rate, across vaccine groups from day 180 to day 360Frequency and severity of solicited local (injection site) and systemic AEs for 7 days post vaccination. The frequency of the following AEs will be reported per regulatory guidance (CPMP/BWP214/96): indurations larger than 50 mm in diameter and persisting for more than 3 days, ecchymosis, temperature >38 °C for 24 h or more, malaise, shiveringPercentage of participants with SAE from day 1 to day 360

### Study schedule, visits and procedures

The study schedule is presented in Fig. 3.

**Fig. 3 Fig3:**
[figure not shown]
Standard Protocol Items: Recommendations for Interventional Trials (SPIRIT) flow diagram of study enrolment, interventions and assessments

### Blood sample analysis

HI and MN antibody testing will be performed by collaborators at a central laboratory. Antibody assays will be performed using standard methods recommended by the World Health Organisation (WHO) [13]. As both assays are subject to considerable interlaboratory variability, assays will be conducted at a single, experienced laboratory using the same technique.

### Influenza surveillance

For all participants, there will be 2-weekly contact (telephone, home visit, or clinic visit) from enrolment to day 360. The method of contact can vary (e.g. telephone, text message, or email); however, there should be participant contact via telephone or face-to-face visit once a month. At each contact, participants will be asked regarding any symptoms meeting protocol definition of an acute respiratory illness, any unscheduled physician visits (e.g. general practitioner, polyclinic, emergency department) or hospitalisations since the previous contact. Participants will also be instructed to contact the study team if they develop any acute respiratory symptoms.

Study investigators will determine whether symptoms meet the European Centre for Disease Prevention and Control (ECDC) definition of an ARI:Sudden onset of symptomsAnd at least one of the following four systemic symptoms:Fever or feverishnessMalaiseHeadacheMyalgia
And at least one of the following respiratory symptoms:CoughSore throatShortness of breathCoryza

If symptoms meet the criteria for an ARI, a study team member will visit the participant to collect a nasopharyngeal swab within 5 days after onset of the illness. Influenza and other respiratory viral pathogens in nasopharyngeal swabs will be detected using a PCR assay. No additional blood samples will be collected during ARI episodes.

### Trial materials

All trial products will be dosed according to Singapore licenses. The vaccine formulation containing the most recent WHO recommendations for strain identity at the start of the trial will be used. Southern Hemisphere winter 2016 and Northern Hemisphere winter 2016/7 recommendations are as below, but may change during the trial:A/California/7/2009 (H1N1)pdm09-like virusA/Hong Kong/4801/2014 (H3N2)-like virusB/Brisbane/60/2008-like virus

Participants will receive one injection of 0.5 ml standard dose, inactivated IIV3 at days 1, and no or one injection at day 180 depending on group allocation. Participants will receive no or one injection of 0.5 ml Tetanus-diphtheria-pertussis vaccine (TDap) at 180 days depending on group allocation.

### Treatment compliance and specific restrictions

The following measures will ensure that the vaccine doses administered comply with those planned, and that any noncompliance is documented so that it can be accounted for in the data analyses. All vaccines will be administered by qualified trial personnel, the person in charge of product management will maintain accountability records of product delivery to the trial site, product inventory at the site, doses given to each participant, and the disposal of unused or wasted doses. Participants will be asked not to take any influenza vaccinations except as provided by the study team for the duration of the study. This restriction will not apply in the event of a national immunisation programme by the Ministry of Health for a pandemic influenza vaccine. There are no restrictions on other vaccines. If prescribed at the same visit they will be administered to a separate body site. There are no limitations on medications, herbs, vitamins, and mineral supplements while participating in the study.

### Safety measurements

AEs, SAEs and ‘Unanticipated Problems Involving Risk to Participants or Others’ (UPIRTSO) events are defined below. Events will be reviewed and graded by the principal investigator (PI) or other investigator. Only members of the study team blinded to participant group allocation will be involved in safety assessment. Severity will be classified using the Common Terminology for Adverse Events version 4.03. The relationship of the event to the study drug, and whether the event is an expected event or not, will be assessed using the list of AEs contained in the product summary of characteristics.

### Adverse event (AE)

An AE is any untoward medical occurrence in a participant administered a trial product. It does not necessarily have a causal relationship with this product. Pre-existing medical conditions are not reported as an AE; an AE may be a new illness, the worsening of a concomitant illness or an effect of vaccination. All AEs include serious and nonserious AEs. Surgical procedures are not AEs; they are the action taken to treat a medical condition. The condition leading to the surgical procedure is the AE, if it occurs during the trial period. AEs will be further categorised as solicited and unsolicited AEs.

A solicited AE is a reaction that is prelisted in the electronic Case Report Form (eCRF). It is defined by nature and time of onset post vaccination, and is considered to be related to vaccination. Unsolicited AEs are all observed AEs which do not fulfil the conditions for a solicited AE, as described above.

### Serious adverse events (SAEs)

A SAE is defined as any untoward medical occurrence that: results in death, is life-threatening (immediate risk of death), requires inpatient hospitalisation or prolongation of existing hospitalisation, results in persistent or significant disability/incapacity, results in congenital anomaly/birth defect, or is a medically important event. Medical and scientific judgment will be exercised in determining whether an event is an important medical event. An important medical event may not be immediately life-threatening and/or result in death or hospitalisation. However, if it is determined that the event may jeopardise the participant and/or may require intervention to prevent one of the other AE outcomes, the important medical event should be reported as serious.

### Collecting, recording and reporting of SAEs to the Health Sciences Authority (HSA)

All SAEs that are unexpected and related to the study drug will be reported to the HSA within 15 calendar days after initial notification to the PI. For fatal or life-threatening cases, the HSA will be notified as soon as possible, but no later than seven calendar days after first knowledge that a case qualifies. A complete report will then follow within eight additional calendar days.

### Collecting, recording and reporting of UPIRTSO events to the National Healthcare Group Domain Specific Review Boards (NHG DSRB)

Any events that are unexpected (in terms of severity or frequency), that can be reasonably attributed to the study drug and that may expose other participants to harm will be reported. A UPIRTSO event refers to problems, in general, that include any incident, experience, or outcome (including AEs) which meet all of the following criteria:Unexpected, in terms of nature, severity, or frequency of the problem as described in the study documentation (e.g. protocol, consent documents, etc.)Related or possibly related to participation in the research. Possibly related means that there is a reasonable possibility that the problem may have been caused by the procedures involved in the research, andRisk of harm. This suggests that the research places participants or others at a greater risk of harm (including physical, psychological, economic, or social harm) than was previously known or recognised

For urgent reporting, all problems involving local deaths, whether related or not, should be reported immediately – within 24 h after first knowledge by the investigator. For expedited reporting, all other problems must be reported as soon as possible but not later than seven calendar days after first becoming known to the investigator.

### Safety assessment methods

To ensure participants’ safety, there will be an immediate post-vaccination surveillance period. Participants will be kept under observation for 15 min after each vaccination. AEs will not be actively solicited during this surveillance period. To collect solicited AEs, all participants will be provided with a safety diary card, a digital thermometer, and a flexible ruler and will be instructed how to use them. The following items will be recorded in the diary card on the day of vaccination and for the next 6 days or until resolution: daily temperature with the route by which it was taken; daily measurement or intensity grade of all other solicited injection site and systemic reactions; action taken for each event (e.g. medication), if any. To collect unsolicited AEs, all participants will be instructed to record any unsolicited AEs that may occur for 7 days after each vaccination. Space will be provided in the diary card for this purpose. AEs which are likely to be related to trial products, whether serious or not, will be followed up by the investigator until their complete disappearance or stabilisation. Information on all SAEs and UPIRTSO events will be collected and assessed throughout the trial, from enrolment until the final study visit (day 360).

### Safety monitoring plan

All vaccines used in this study are part of routine vaccination schedules. Safety data has been established from millions of administered doses. According to the WHO, the incidence of vaccine-related SAEs, such as anaphylaxis and GBS, is approximately 1 per million doses. The rate of mild, nonsevere AEs in clinical trials is similar between influenza vaccine and placebo. Vaccine-related SAEs are not expected in a clinical trial of this size. AEs will be monitored for the first 7 days after each vaccination. SAEs will be monitored for the first 28 days after each vaccination. An interim safety analysis will not be performed. The study team will review any UPIRTSO events and stop the trial if significant risk to participants from continuing in the trial is suspected.

### Data entry and storage

Paper Case Report Forms (CRFs) will be used for initial data collection. These will be transcribed to an eCRF developed with an independent web-based hosting facility called Research Electronic Data Capture (REDCap). The trial database will include information on demographics (age, gender), underlying illnesses, concomitant medications and vaccination history. AE and SAE data will also be entered. Paper documents will be maintained and stored in a locked office, with access restricted to study personnel. All electronic documents with participant information will be password-protected.

### Data quality assurance

A random sample of source documents and CRFs will be audited to substantiate the integrity of trial data entered into the electronic database.

### Sample size calculation

The following assumptions were made for determination of sample size expected to meet primary outcome:Rate of seroprotection (HI antibody titre ≥1:40) on day 208 after vaccination is 60%Proportion seroprotected at day 208 in the experimental group will be 80%A loss to follow-up rate of 10%A power (1 − *β*) of 80% to detect differences between the two primary study groupsA two-sided significance level (*α*) of 5%

The primary statistical null hypothesis is of no increase in seroprotection rates (HI antibody titre ≥1:40) at day 208 following booster IIV3 vaccination, compared to a control injection. Formally, the trial will test:H_0_: Seroprotection rate (booster) = seroprotection rate (control), versusH_A_: Seroprotection rate (booster) ≠ seroprotection rate (control)

A sample size of 164 (82 per group) will provide 80% power to test this hypothesis, based on approximations to the normal distribution. A total sample size of 200 (100 per group) has been chosen to allow for up to 15% dropout. This sample size will provide adequate power for a range of seroprotection rates assuming an increase in absolute seroprotection of at least 20%.

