**Discussion:**

If superiority of 6-monthly influenza vaccination is demonstrated, this study could form the basis for a larger clinical trial with influenza infection as the primary endpoint.

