### Statistical analysis

The full analysis set (FAS) consists of all participants who received at least one injection. Participants will be analysed according to the group to which they were randomised. The per-protocol analysis set (PPS) is a subset of the FAS who have no major protocol violations. Participants presenting with at least one of the following protocol deviations will be excluded from the per protocol analysis: participant did not meet all protocol-specified inclusion criteria or met at least one of the protocol-specified exclusion criteria; participant did not complete the vaccination schedule; participant received a different vaccine than the one randomised to receive; participant did not receive vaccine within the protocol-determined time window; participant received additional seasonal trivalent influenza vaccines during the trial period; preparation and/or administration of the vaccine was not performed as per protocol.

The safety analysis set is defined as those participants who have received at least one vaccine. All participants will have their safety analysed according to the vaccine that they actually received. The FAS will be the primary analysis to infer superiority of a 180-day IIV3 booster vaccination compared to the active-comparator control in terms of the proportion of participants with day-208 HI antibody titres ≥1:40. This will be supported by per-protocol analysis. Analysis of secondary endpoints will use both the FAS and PPS.

Immunological data will be analysed per CHMP guidance (EMA/CHMP/VWP/457259/2014). Results will be presented by vaccine strain and will include GMTs (with 95% confidence intervals) and pre-/post-vaccination ratios (GMRs). Reverse cumulative distribution curves will also be provided, supplemented by tables presenting percentages of vaccinees with titres above a range of cut-off levels on a logarithmic scale.

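### The primary outcome covers three vaccine strains, but alpha and power are set for one comparison and no rule says how the strains combine into the single superiority claim.

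*Protocol article*

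**What the plan says.** All references are to the protocol article.

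- **Primary outcome:** the percentage seroprotected "at day 208 post primary vaccination for each of the influenza strains present in the administered influenza vaccine". The primary objective is also worded strain by strain. Trial materials lists three strains: one A/H1N1, one A/H3N2 and one B.
- **Sample size calculation:** one pair of rates (60% control, 80% booster), one two-sided 5% level, one 80% power and one null hypothesis that names no strain ("Seroprotection rate (booster) = seroprotection rate (control"). The result is: "A sample size of 164 (82 per group) will provide 80% power to test this hypothesis, based on approximations to the normal distribution". Enrolment is 100 per group, to allow for up to 15% dropout.
- **Statistical analysis:** "The FAS will be the primary analysis to infer superiority of a 180-day IIV3 booster vaccination compared to the active-comparator control". Results are to be presented by strain, but nothing says whether the inference needs one strain, all strains or a separate conclusion for each.
- **Abstract, Discussion:** the follow-on trial is introduced with "If superiority of 6-monthly influenza vaccination is demonstrated", again in the singular.

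**The concern.** Three strain comparisons feed one stated conclusion, yet the error rate and power are those of one comparison. What 5% and 80% mean then depends on a rule the article does not give. If one significant strain is enough, the trial has three chances at a false positive. If every strain must succeed, it has three chances to miss.

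This matters because it concerns the confirmatory analysis. If the rule is not fixed before unblinding, a mixed result (one strain significant, two not) could be reported either as superiority or as failure, and the plan would not say which. The result is also meant to motivate a larger infection trial, so readers will want to know how strong the evidence behind the word superiority is.

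**Working it through.** **Inputs from the article.** Control rate 0.60, booster rate 0.80, two-sided alpha 0.05, power 0.80 and 1:1 allocation (Sample size calculation; Summary of study design). Three strains (Trial materials). Evaluable size is 82 per group, or 100 × (1 − 0.15) = 85 per group after the stated 15% dropout.

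**Inputs assumed.** The article gives no strain-specific rates and no between-strain correlation. I take 60% against 80% for every strain and an equal latent Gaussian correlation of 0 to 0.7 between a participant's three titres.

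**Step 1: reproduce the plan's figure.** Pooled normal approximation, mean rate 0.70:

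n = [1.960 × √(2 × 0.70 × 0.30) + 0.8416 × √(0.60 × 0.40 + 0.80 × 0.20)]² / 0.20²
= (1.270 + 0.532)² / 0.04 = 81.2, so 82 per group and 164 in total.

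This matches exactly. Power at 82 is Φ[(0.20 − 1.960 × √(0.42/82)) / √(0.40/82)] = Φ(0.855) = 80.4%. The stated size is therefore that of one test at the undivided 5%.

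**Step 2: independent strains, by hand.**

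- Any strain, two-sided familywise error: 1 − 0.95³ = 14.3%.
- Any strain, false claim favouring the booster: 1 − 0.975³ = 7.3%, against a nominal 2.5%.
- Any strain, power at 82 per group: 1 − (1 − 0.804)³ = 99.2%.
- All strains, power at 82 per group: 0.804³ = 51.9%.

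**Step 3: correlated strains, by simulation.** Binary outcomes were cut from correlated normals and each strain tested by the pooled z-test. Each range covers latent correlation 0 to 0.7.

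| Success rule | Error rate | Power |
|---|---|---|
| Any strain, each at unadjusted 5% | about 14% falling to 12% two-sided; 7% to 6% favouring the booster | 99% to 96% at 82 per group |
| All three strains, each at 5% | at or below 5% | 53% to 62% at 82; 55% to 64% at 85 |
| Separate strain claims, unadjusted | 5% for each strain | about 80% for each strain |
| Holm across three, claims by strain | familywise 5% | averaged over strains 74-78%; at least one 88-97%; all three 51-62% (82-85 per group) |

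The simulated all-strain power under independence is about one point above the hand value because the hand value uses the normal approximation.

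**Step 4: a stronger dependence.** With a correlation of 0.9 between the test statistics themselves, which is beyond the range above, the normal approximation gives 8.3% any-strain error (4.1% favouring the booster) and 72.6% all-strain power at 82 per group. The gaps narrow but do not close.

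**The case against.** **The text supports strain-by-strain conclusions.** The primary objective and primary outcome are both worded per strain, and results are to be presented by strain. On that reading each comparison has its own 5% and about 80% power, and whether separate claims also need familywise control is partly convention. This stands as a possible reading. But the inferential sentence in Statistical analysis speaks of superiority of the booster as one conclusion, and three separate claims do not deliver that.

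**Multiplicity rules often sit in the SAP or full protocol, which are not shown.** The article also refers to CHMP guidance for the immunological analysis. This is fair for the adjustment method, and its absence alone would be no finding. But the article itself fixes the hypothesis, alpha, power and size for a single comparison. A rule placed elsewhere cannot make 80% true of an all-strain claim, or an undivided 5% true of an any-strain claim.

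**Stronger readings that do not hold.** A reader might infer that the superiority claim has lost both its error rate and its power. No single rule does that: any-strain inflates error while power exceeds 80%, and all-strain costs power while error stays controlled. A reader might also take 14.3% as the chance of falsely declaring the booster better. It counts differences in both directions, and the figure for a false pro-booster claim is about half of it. Finally, the discussion passages might be read as a formal go/no-go criterion for the next trial. They are conditional remarks on motivation and set no criterion.

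**Conclusion.** The concern holds as an undefined success rule. The sample size is correct for one comparison, the primary outcome has three, and one overall superiority is inferred from them. Depending on the rule adopted, either the 5% is exceeded (about 12-14% two-sided, about 6-7% in the booster's favour against 2.5%) or the 80% is not reached (about 53-64% for all three strains at 82-85 per group). Separate strain claims keep both figures, at the price of having no single conclusion.

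The joint figures rest on equal 60% against 80% rates in every strain and a latent correlation of 0 to 0.7. Both are assumptions, so the ranges should be read as indicative. The mismatch itself does not depend on them.

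Severity: should-fix. The remedy is short and leaves the design intact.

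**What to change.** In Sample size calculation, write the null hypothesis for each strain. There and in Statistical analysis, state one success rule and the power that goes with it. Either of these would do:

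1. **Holm, with claims by strain.** Control the three strain tests at a two-sided familywise 5% by Holm's procedure and claim superiority only for the strains that pass. Restate power as about 74-78% averaged over strains, about 88-97% for at least one strain and about 51-62% for all three.
2. **All three strains required.** Claim overall superiority only if every strain is significant at two-sided 5% in favour of the booster. No alpha adjustment is needed. Restate power as about 53-64%.

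Give the assumed rates and between-strain correlation beside whichever figures are used, and word the superiority sentence in Statistical analysis and the abstract to match the rule.

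Cost: a few sentences in the protocol and SAP, with no change in sample size, participants or blood samples. The downside is that the stated power becomes less favourable than 80%.
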